## Abstract

**Background:**

To determine the effectiveness of reminders compared to no reminders in improving adherence to multiple clinical recommendations measured as the resolution of the clinical condition that motivated the reminder, in a primary care setting with a well-established feedback system.

**Methods/design:**

A 12-month, cluster-randomized, controlled clinical trial was designed (randomized by primary care team) to evaluate the impact of computerized reminders. All study participants will continue to receive the usual feedback from the electronic health records system. The control group (well-established feedback) will be compared with reminders and a well-established feedback system. The study will include all general practitioners (3425) and nurses (3262) providing primary care for a population aged 14 years or older in the 282 primary care teams reporting to the Catalan Institute of Health. Up to 10 clinical reminders are offered for each patient, recommending action related to at least one of nine clinical conditions: arterial hypertension, elevated cardiovascular risk, type 2 diabetes mellitus, cerebrovascular accident, ischemic heart disease, heart failure, atrial fibrillation, smoking habit, and hepatitis C. The outcomes are the resolution of the clinical condition that motivated the reminder and the time elapsed between the first reminder message and implementation of the recommended action (months). Due to the obvious correlation between reminders about the same patient, the profile of patients assigned to a particular professional, and the professionals assigned to a particular centre, hierarchical modelling will be used to simultaneously estimate the effect of the study variables at these different levels of analysis. To estimate the impact of the intervention arm, an analysis of adherence to each type of reminder will be carried out, using multi-level logistical regression models at level of the primary care centre. Time to adherence will be estimated by the Kaplan–Meier method and comparisons will be done using the log-rank test.

**Discussion:**

The results of this study could provide new evidence on the impact of computerized reminders at the point of care on adherence to clinical guidelines in primary care with an established feedback system.

*Trial registration* ISRCTN42391639. October 8, 2012

## Background

Computerization of medical records and the availability of computer access in all medical offices in the primary care setting have made it possible to study the impact of this computerization in daily clinical practice (Fina et al. 2006). The Catalan Institute of Health (*Institut Català de la Salut*, ICS) is the main public provider of primary care services in the National Health System of Catalonia, with 282 primary care teams serving nearly 6 million people (80 % of the Catalan population). The 8000 health professionals comprising these teams provide family, paediatric, and nursing care. Since 2005, all ICS primary care providers have used the same electronic health records system, called ECAP, and since 2006 have been able to access a feedback system, updated monthly, that reports on quality indicators evaluating the care provided. All professionals have access to their rates of adherence to the evaluation standards and can view detailed information at the patient level. The feedback system also compiles a list of patients who do not meet all established criteria of the 62 evidence-based recommendations that constitute a unique index known as the Quality of Care Standard (*Estàndard de Qualitat Assistencial*, EQA). At present, health professionals have point-of-care access to all of these results, with no additional data-recording effort on their part (Coma et al. 2013).

Primary health care allows longitudinal follow-up of a population. It also requires attention to multiple health conditions and disease prevention activities in a relatively brief office visit. Bodenheimer estimated that a primary care physician would require 18 h per workday to implement all of the prevention activities recommended by experts in chronic diseases (Bodenheimer 2008). Given the multitude of recommendations, it would be of great interest to health care professionals to have tools available that would help them carry out evidence-based activities. One of the strategies used to improve clinical practice is the incorporation of recommended activities as reminders in the clinical record (Jamtvedt et al. 2003).

The availability of the shared electronic health record allows electronic reminders at the point of care, which has been associated with an improvement in clinical practice, estimated at 4.2 % (interquartile range 0.8–18.8 %). This wide variability could be explained by differences in the settings where the studies were carried out, the basal levels of adherence, or the characteristics of the reminders studied (Shojania et al. 2010).

Most of the randomized clinical trials that have evaluated the effectiveness of reminders in the primary care setting have included reminders for just one disease or clinical condition (Eccles et al. 2002; Filippi et al. 2003; Flottorp et al. 2002; Hicks et al. 2008; Krall et al. 2004; Safran et al. 1995; Sequist et al. 2005; Tierney et al. 2003; van Wyk et al. 2008). The studies that have included interventions with multiple reminders have focussed on preventive measures such as vaccinations and screenings or potential adverse effects of medications (Frank et al. 2004; Tamblyn et al. 2003).

In a retrospective analysis, an association was observed between the level of adherence to the recommendations of interest and the frequency of accessing the feedback provided and the patient list. In other words, the professionals who consulted their own quality results and the status of their patient lists showed greater improvement in their clinical indicators than their colleagues who did not consult the feedback results; in addition, a temporal relationship was detected between the availability of feedback and the clinical improvement (Fina et al. 2006). Even though different clinical trials have studied the impact of paper reminders and other interventions such as economic incentive or educational support materials, there is a lack of scientific evidence on the impact of computerized reminders (Shojania et al. 2010).

In 2012, a maximum of 10 computerized reminders per patient was introduced into the ECAP system, visible to the health professional during the patient visit and related to 25 of the 62 recommendations considered as quality indicators in the EQA. We designed a clinical trial to evaluate whether adding computerized reminders to a well-established feedback system would improve adherence to multiple clinical recommendations in the primary care setting.

### Research hypothesis

The hypothesis was that computerized point-of-care reminders (i.e., presented during the contact between a primary care professional and a patient) improve the level of adherence to the recommended action and reduce the time to implementation of the recommendation.

### Objectives

#### Primary objectives

To determine the effectiveness of reminders compared to no reminders in improving adherence to multiple clinical recommendations measured as the resolution of the clinical condition that motivated the reminder, in a primary care setting with a well-established feedback system.

#### Secondary objectives

To describe the effectiveness of the three levels of reminders intervention: (1) pop-up reminder, (2) pop-up reminder and a calendar icon, and (3) pop-up reminder, calendar icon, and configurability (users can select how the reminders are shown).

To describe resolution and time to resolution of the reminders by type of professional, primary care team and by each of the reminders in improving adherence to the clinical recommendations contained in the reminders.

To compare the effectiveness of computerized reminders in improving adherence to multiple clinical recommendations by category (primary, secondary and tertiary prevention).

To compare the effectiveness of computerized reminders in improving adherence to multiple clinical recommendations by category (professional action only and the professional action plus the modification of patient behaviour).

## Methods

### Study design

The study is a controlled clinical trial, cluster-randomized by primary care team, designed to evaluate the impact of computerized reminders on adherence to clinical recommendations in a primary care setting with an established feedback system. A pilot study will conducted with primary care centre (PCC) health professionals to improve the development of the reminders. During the clinical trial, all of the study participants, including the control group, continued to receive the usual feedback. The control group is compared with each of the three study arms: (1) pop-up reminder, (2) pop-up reminder and a calendar icon, and (3) pop-up reminder, calendar icon, and configurability.

### Study population

The inclusion criteria are: being a family physician or nurse who care for adult patients aged 14 years of older with clinical conditions that could generate at least one of the reminders in one of the 282 primary care teams managed by ICS. The exclusion criteria are: professionals who did not adopt the reformed model of primary care defined in Spanish legislation will be excluded due to low utilization of the electronic health record (Real Decreto 137/1984). Furthermore professionals of a primary care team participating in other clinical trials of electronic health record reminders, and those that participate in the pilot stage of this clinical trial will be excluded. It is important to emphasize that this is a global intervention involving all ICS health professionals. The analysis will take into account all included professionals in each PCC (or cluster).

#### Control group

During the clinical trial, all study participants, including those in the control group, will continue to receive the usual feedback established in 2006. This feedback consists of a monthly update for each family physician and primary care nurse of their percentage of adherence to each of the evidence-based recommendations in the EQA, along with a comparison of the month’s results with their own basal data, with the rest of their team, and with the mean of all ICS teams.

For ease of interpretation, the results will be color-coded by target values. For 20 of the 25 recommendations, in addition to the numerical score, professionals will be able to consult the list of patients who do not meet the target; the goal is that the professional will review and take action with those individuals. Access to the feedback screen is provided as a direct link within the electronic health record (Figs. 1, 2, in Catalan; an online demonstration of this feedback system is available at: http://www.amf-semfyc.com/sisap/) (Coma et al. 2013). The monthly results are also used as part of a performance incentive variable in the compensation model; during the intervention year, the incentive will not exceed a total of 750 euros per physician and 380 euros per nurse.

**Fig. 1 Fig1:**
[figure not shown]
Feedback screen that can be accessed by health professionals from the electronic health records system. Well-established feedback without reminders (control group)

**Fig. 2 Fig2:**
[figure not shown]
Detail of the feedback screen to which health professionals have access. Well-established feedback without reminders (control group)

In contrast to the intervention with point-of-care reminders that will be evaluated using the present protocol, the usual monthly feedback screen (control group) does not allow direct interaction with the clinical health record system; this feedback is associated with the professional, not the individual patients, and requires that the health professional actively seek out the numerical results or the patient lists from which the established feedback screen draws the relevant data.

### Intervention

A maximum of 10 clinical reminders per patient will be offered, recommending actions related to at least one of the following nine clinical conditions: arterial hypertension, elevated cardiovascular risk, type 2 diabetes mellitus, cerebrovascular accident, ischemic heart disease, heart failure, atrial fibrillation, smoking habit, and hepatitis C. The reminders are integrated into the electronic health record for each patient so that they are available to any health professional who cares for the patient; the information is updated weekly to reflect any changes that occur.

Each reminder consists of the following information: an orange or red icon that codes the importance of the recommendation as moderate or high, respectively; the relevant clinical condition; the recommended action; and the date and value entered for the recommendation or related laboratory results. A recommendation is classified as highly important if treatment is required (red icon: e.g., atrial fibrillation, anticoagulant/antiplatelet treatment, 12/06/2011) and as moderately important if it refers to a variable, laboratory result, or vaccination (orange icon: e.g., Type 2 diabetes mellitus, monitor HbA1c, most recent value, 8.3, 12/05/2011) (Table 1).

**Table 1 Tab1:** Recommendations, clinical conditions, importance and estimated number of reminders

Recommendation (http://www.gencat.cat/ics/professionals/guies/mpoc/mpoc.htm)	Clinical condition	Importance	n (estimated)
Control blood pressure: ≤140/90 or ≥150/95, depending on risk status	Arterial hypertension/elevated cardiovascular risk	Moderate	534,702
Control glycaemia: HbA1c ≤ 8 %	Type 2 diabetes mellitus	Moderate	92,520
Control cholesterol: LDL < 120	Cerebrovascular accident/Ischemic heart disease	Moderate	90,060
Screen for retinopathy	Type 2 diabetes mellitus	Moderate	67,710
Smoking cessation within past year	Smoking habit	Moderate	711,392
Vaccination for hepatitis B	Hepatitis C	Moderate	14,534
ACEI/ARA2 treatment	Heart failure	High	11,394
Beta blockers treatment	Heart failure/Ischemic heart disease	High	69,155
Antiplatelet/anticoagulant treatment	Atrial fibrillation	High	16,260
Antiplatelet treatment	Cerebrovascular accident/Ischemic heart disease	High	12,916

*Hb* haemoglobin, *LDL* low-density lipoprotein, *ACEI* angiotensin-converting enzyme inhibitor, *ARB* angiotensin II receptor blocker

Health professionals can also choose to view the reminders in their daily schedule of patients. The reminder provides a link to the patient’s electronic health record, from which the pertinent action can be taken (generate a prescription, record a vaccination, request a laboratory test, or record a clinical variable). There is also an option to ignore or exclude a recommendation for a particular patient and enter a comment about the reason for the exclusion.

#### Randomization

The PCC will be the unit of analysis, so that all professionals from the same centre will be assigned to the same arm of the trial. Randomization will be done with the Stata/SE (v. 11.2, StataCorp) module for the design of randomized clinical trials (Ryan 1990). With the goal of achieving a balanced distribution of the quality of care by PCC in each arm, centres will be stratified by the quintiles of EQA results in the month prior to study initiation. The procedure will consist of obtaining the ICS list of PCCs, importing the data in STAT format, applying the inclusion and exclusion criteria, and adding the EQA value for each PCC. The PCCs will be allocated in randomized blocks of 6, 12, and 18 to achieve the same number of PCCs in each of the study groups (Fig. 3).

**Fig. 3 Fig3:**
[figure not shown]
Algorithm for the randomization to each study group

#### Intervention groups

The reminders can appear in the electronic health record screens in 3 levels. Each intervention group will receive a distinct, incremental presentation of the reminders: pop-up only, pop-up plus calendar icon, and pop-up plus calendar icon, with a customizable option.Pop-up windowHealth professionals allocated to this group will access a patient’s electronic health record; if a reminder has been generated for that patient, a pop-up window will present all of the patient reminders. No other display option will be available. The pop-up appears automatically to the professional on accessing the patient record from their calendar list of patients with an appointment. Before entering any other information they have to close the pop-up or click on the reminder to address the issue.Pop-up + calendar iconEach health professional has an online calendar with the list of patients scheduled for the day. The professionals allocated to this arm will be alerted to any reminders pertaining to each patient on the daily schedule. A square orange or red icon will appear next to the patient’s name, indicating the most important reminder (moderate or high) generated, with a small number showing the total number of reminders for that patient. This icon will be linked to the patient’s electronic health record with the pop-up window described for the first study arm.This level of intervention (in addition to just the pop-up window) gets a calendar icon. As for the pop-up, health professionals sees this window every time they access the patient’s record from the appointments calendar, the content of the pop-up being the unaddressed reminders, As for the calendar icon, the professionals see them every time they navigate to the calendar list of patients with an appointment.Configurability (pop-up + calendar icon + configuration options)The default configuration will show all reminders generated for a specific patient. Health professionals allocated to this group will be able to modify the default configuration, adding filters to select only the reminders they want to see integrated into the electronic health record. This option will be added to the pop-up window (which will still allow access to the expanded list of reminders) and the calendar alerts (which will continue to indicate the total number of reminders generated). Screenshots and detailed description of the intervention (Fig. 4).

**Fig. 4 Fig4:**
[figure not shown]
Detail of the one type of intervention screen (pop-up window) to which health professionals have access

#### Length of the intervention

The trial is designed to last one year. After 6 months, the main outcome variable will be analysed and the study will be halted if there is more than 10 % difference between the control group and any of the intervention groups.

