### Sample size

A 10 % difference between the proportion of resolved reminders and the assumed proportion in the intervention group of 59 % will be considered clinically relevant (Demakis et al. 2000). Assuming an alpha error of 0.01, 95 % power, and 10 % loss to follow-up, and correcting for an intraclass correlation in the PCCs of 0.05, each of the 4 study groups will require 15,950 reminders, a total of 63,800. The estimated number of reminders to be generated is shown in Table 1. Nonetheless, due to the design of the computerized tool, the need for cluster randomization, and the availability of the universal sample, it is not considered necessary to limit the study to the calculated sample size.

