### Study oversight

There isn’t an independent data monitoring or trial steering committee.

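### The 6-month rule halts the whole trial on a point difference above 10% in any one arm, the same figure as the design difference; a halt is more likely than not if all three arms truly differ from control by about 9 points or more at month 6

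*Protocol article*

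**What the plan says.** The section on the length of the intervention first fixes the duration: "The trial is designed to last one year". It then adds one look. At six months, it says, "the main outcome variable will be analysed and the study will be halted if there is more than" a fixed amount. That amount is 10%, and it applies to the "difference between the control group and any of the intervention groups". What is halted is the study, not an arm. The rule names no test, confidence limit or direction.

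The sample size section uses the same figure. It takes 10% as the "difference between the proportion of resolved reminders and the assumed proportion in the intervention group of" 59%, and says that a gap of this size "will be considered clinically relevant". It does not say at what month this difference is expected. The Discussion repeats 10% as the chosen clinically relevant effect, and also says that the existing feedback system may make the effect smaller.

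The study oversight section says that there is not "an independent data monitoring or trial steering committee". The main outcome has two parts, the proportion resolved and the months from first reminder to action. The study design section compares each of the three formats with control, and a secondary objective is "To describe the effectiveness of the three levels of reminders intervention".

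**The concern.** A threshold placed at the design difference sits at the centre of the sampling distribution when that difference is real. Chance then decides whether the second half of the trial takes place. Any one of three arms can trigger the halt, and the halt stops all of them. A difference against reminders would count as well as one in their favour, because no direction is given.

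At stake are months 7 to 12 of follow-up in every arm: resolution at 12 months, the later part of time to resolution, and the description of the three formats over the planned year. Whether an early effect lasts would not be seen. No independent body is in place to apply or interpret the rule.

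**Working it through.** **Inputs.** From the protocol: 59% in the intervention group and a 10% difference, read here as 49% versus 59%; ICC 0.05; 282 teams before exclusions; four equal groups; alpha 0.01, power 95% and 10% loss. Assumed: k = 282/4 = 70.5 centres per arm, with 52 as a low end to allow for exclusions. Reminders per centre, m, are not stated. I take 228 (63,800 over about 280 teams) up to 5,747 (the Table 1 total of 1,620,643 divided by 282), and 305 for the case with 52 centres.

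**The protocol's own figure.** For 59% versus 49%, two-sided alpha 0.01 and 95% power, the usual formula gives 882 per arm; 882/0.90 = 980. With an assumed 300 reminders per centre, 1 + 299 × 0.05 = 15.95, and 980 × 15.95 ≈ 15,630, within about 2% of the stated 15,950. So 49% versus 59% is a plausible reading. The mean cluster size is not given, so the figure cannot be confirmed.

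**Standard error of one arm versus control.**

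SE = √{[0.59×0.41 + 0.49×0.51] × [1 + (m−1)×0.05] / (k×m)}

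- k = 70.5, m = 5,747: √(0.4918 × 0.05017 / 70.5) = 0.0187
- k = 70, m = 228: 0.0195
- k = 52, m = 305: √(0.4918 × 0.05311 / 52) = 0.0224

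The SE is therefore 1.9 to 2.2 points, and 10 points is 4.5 to 5.3 SE.

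**Chance of a halt.** Three arm differences sharing one control were simulated with 2 million draws. The ranges span the three k, m settings above.

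| True difference at month 6 | P(halt) |
|---|---|
| 10 points in all three arms | 75% |
| 10 points in one arm, 0 or 5 in the others | 50% |
| 9 points in all arms | 53-56% |
| 8 points in all arms | 30-37% |
| 5 points in all arms | 1-3% |
| none | below 0.01% |

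The 75% can be checked by hand. When every true difference equals the threshold, no arm crosses only if the control group's sampling error is the largest of four nearly exchangeable errors, which has probability 1/4. All three cross only if it is the smallest, again 1/4. So P(halt) = 3/4, whatever the SE. Among halts, (3/4 − 1/4)/(3/4) = 2/3 include at least one arm that has not crossed; the simulation gives 66%.

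**If the 10 points belong to month 12.** With a constant resolution rate, the month-6 proportions are 1 − √0.51 = 28.6% and 1 − √0.41 = 36.0%, a gap of 7.4 points. P(halt) is then 16-24%. For 59% versus 69% the month-6 gap is 8.4 points and P(halt) is 37-43%.

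**Selection of the estimate.** Given a halt at a true 10 points in all arms (k = 70.5), the best arm averages 11.8 and the mean over the three arms is 10.6. With 52 centres these are 12.2 and 10.7. Even without a halting rule, the best of three arms would average 11.1.

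**The case against.** The strongest reply is that the rule is hard to trigger unless the effect is large. The Discussion expects the feedback system to shrink the effect, and at 5 points a halt has a chance of only 1-3%. In a trial of this size, 10 points is also far more demanding than a conventional p-value boundary. Stratification by quality-of-care quintile should reduce the SE somewhat, which lowers the halt probabilities below 10 points. All of this stands, and it limits how often the rule would bite.

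Four stronger readings are tempting, but the documents do not support them:

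- **That the hypothesised effect would most likely end the trial.** This needs about 9 points or more at month 6 in all three arms. The sample size section does not date its 10%.
- **That the reported effect would be badly inflated.** At a true 8 points, the best arm given a halt averages 11.1, which is 38% too high. But the best of three averages 9.1 with no halt at all, the three-arm mean given a halt is about 9.7, and nothing says the best arm would be the reported estimate.
- **That the rule raises false positives.** Under no effect, halting is negligible.
- **That the interim figure ignores clustering.** The rule says only that the main outcome will be analysed, and the statistical section plans hierarchical models for it. What is missing is a criterion of precision for the halt.

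A halt would also leave six months of data on all arms, so the comparison of formats is shortened, not lost.

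None of this answers the central point. The rule as written stops arms that have not crossed, at a threshold equal to the design difference, on a point difference alone.

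**Conclusion.** The concern holds in a conditional form. The rule ends follow-up in all arms at month 6 with probability 75% if all three arms truly differ by 10 points by then, and 50% if only one does. The chance is about a third at 8 points, 16-24% if 49% versus 59% accrues steadily to month 12, and a few per cent or less at 5 points. The main cost is months 7 to 12 for every arm. Bias is secondary: at a true 10 points, about 0.6 points on the three-arm mean and 1.8 on the best arm.

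These figures assume about 70 centres per arm (52 at the low end), ICC 0.05, percentage points rather than relative change, and no gain from stratification. The 75% and 50% do not depend on the SE, because they follow from setting the threshold at the true difference. The other rows do depend on it.

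**What to change.** Delete the efficacy halt and run the planned twelve months.

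If the six-month look is kept:

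- reconcile it with the sample size section by stating the month to which the 10% refers, whether it is absolute, and its direction;
- require the lower confidence limit of the cluster-adjusted difference, not just the point estimate, to exceed the 10-point criterion. With a 95% interval and SE 1.87 the observed difference would have to pass 10 + 1.96 × 1.87 = 13.7 points. A limit that need only exceed zero would be met at 3.7 points, looser than the present rule;
- let the rule affect only the arm concerned;
- continue data collection in all arms to month 12, and name the 12-month result as the reported estimate.

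A p<0.001 boundary is not a safe substitute. It would be crossed at 3.29 × 1.87 = 6.2 points for one arm. For pooled reminders versus control, the SE is 1.87 × √(2/3) = 1.53, and the boundary falls at 5.0 points. At a true 8 points the pooled boundary would be crossed about 97% of the time, against about 30% for the present rule, and a pooled contrast cannot act on one arm only.

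The cost is one protocol paragraph. The downside is that control centres may wait up to six more months for the tool if it works, while keeping their usual feedback.
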